# Exercise effects on functional capacity and quality of life in older patients with colorectal cancer: study protocol for the ECOOL randomized controlled trial

**DOI:** 10.1186/s12877-023-04026-6

**Published:** 2023-05-22

**Keywords:** Training, Physical therapy, Colon, Prehabilitation, Rehabilitation, Ageing

## Abstract

**Background:**

Surgery and treatment for colorectal cancer (CRC) in the elderly patient increase the risk of developing post-operative complications, losing functional independence, and worsening health-related quality of life (HRQoL). There is a lack of high-quality randomized controlled trials evaluating the potential benefit of exercise as a countermeasure. The primary aim of this study is to evaluate the effectiveness of a home-based multicomponent exercise program for improving HRQoL and functional capacity in older adults undergoing CRC surgery and treatment.

**Methods:**

This randomized, controlled, observer-blinded, single-center trial aims to randomize 250 patients (>74 years) to either an intervention or a control group (i.e., usual care). The intervention group will perform an individualized home-based multicomponent exercise program with weekly telephone supervision from diagnosis until three months post-surgery. The primary outcomes will be HRQoL (EORTC QLQ-C30; CR29; and ELD14**)** and functional capacity (Barthel Index and Short Physical Performance Battery), which will be assessed at diagnosis, at discharge, and one, three, and six months after surgery. Secondary outcomes will be frailty, physical fitness, physical activity, inspiratory muscle function, sarcopenia and cachexia, anxiety and depression, ambulation ability, surgical complications, and hospital length of stay, readmission and mortality.

**Discussion:**

This study will examine the effects of an exercise program in older patients with CRC across a range of health-related outcomes. Expected findings are improvement in HRQoL and physical functioning. If proven effective, this simple exercise program may be applied in clinical practice to improve CRC care in older patients.

**Trial registration:**

ClinicalTrials.gov ID: NCT05448846.

**Supplementary Information:**

The online version contains supplementary material available at 10.1186/s12877-023-04026-6.

## Background

Colorectal cancer (CRC) is the second most common cancer and the second leading cause of cancer-related mortality in Europe [1]. CRC is more frequent in older than in younger people (31% of affected patients are ≥75 years) [2] and its global prevalence is projected to increase by 2040, especially among older people due to population ageing [3]. Moreover, the expansion of unhealthy lifestyle-related risk factors like westernized diet, obesity, and physical inactivity are contributing to the increase of CRC burden [4].

Tumor resection through surgery is considered the cornerstone of CRC treatment, whereas advanced age is an independent predictor of post-operative mortality and complications [5]. Among older patients undergoing CRC surgery, the presence of geriatric syndromes (e.g., frailty, cognitive and functional impairment) worsens prognosis and increases the risk of developing post-operative complications [6]. Likewise, a recent study has suggested that CRC patients with low muscle mass and muscle quality are more likely to suffer complications after surgery [7]. This is especially relevant in people over 75 years of age, since age-related loss of muscle mass and strength is accentuated [8]. Moreover, the high prevalence of cancer-related cachexia in older people with CRC (approximately 60% in people aged 70 or older) [9] makes this population particularly vulnerable to loss of muscle mass, strength, and physical function (i.e., sarcopenia). Indeed, physical function usually remains below baseline values from three and up to six months following CRC treatment, which could lead to permanent dependency for self-care activities in over half of the older patients [10]. Thus, older patients are at high risk of losing functional independence after CRC treatment.

In older people, a decline in intrinsic capacity (i.e., the composite of all the individual’s physical and mental capacities) increases the risk of functional impairment (i.e., the loss of the individual’s ability to perform activities of daily living (ADLs) independently) and may undermine their health-related quality of life (HRQoL) [11]. In CRC older patients, HRQoL is commonly constructed by disease-specific outcomes (e.g., side effects of surgery and/or radiotherapy, toxicity of systemic therapy, fatigue, pain, bowel functioning) together with other concerns regarding geriatric syndromes and preferences (e.g., functional capacity, social functioning, mood, participation in decision making) [12]. Integration of HRQoL assessment and promotion into care, treatment and follow-up is especially important in older patients with cancer since some of them weight HRQoL over a survival gain compared to younger individuals [13]. Moreover, owing to the improvements in early detection and treatment of CRC, survival has substantially progressed up to 66% at 5 years [14]. Accordingly, there is an increasing number of people living with CRC-related sequelae that threaten their HRQoL [15]. In this regard, the implementation of complementary interventions to anticancer treatments to promote HRQoL and to minimize the consequences of accelerated aging induced by these treatments are warranted [16, 17].

The regular practice of physical activity (PA) in cancer patients has been associated with a better HRQoL [18–23], physical function [21, 24] and functional capacity [18]. PA also contributes to reduce mortality risk [25, 26] and muscle atrophy [27, 28]. In this sense, the World Health Organization [29] and the American Cancer Society [30] recommend performing at least 150-300 minutes per week of moderate-intensity PA or 75-150 minutes per week of vigorous-intensity PA (or a combination thereof) involving resistance and endurance exercise – as well as minimizing sedentary behaviors – for primary and tertiary cancer prevention in adults. Moreover, the benefits of physical exercise as an intervention for promoting healthy ageing and treating age-related disorders in older patients with cancer are well documented [20, 21]. However, there is high inter-individual variability on the effects of exercise interventions that can be explained by several factors such as type of cancer, participants’ or interventions’ characteristics, or type of study. Studies on exercise effects in elderly patients with CRC are scarce and methodologically heterogeneous. A recent review [5] which included 11 randomized controlled trials (RCT) concluded that exercise interventions improve functional capacity [31–33] and reduce postoperative complications [34, 35] and length of hospital stay (LOS) [35, 36] in CRC patients with surgical indication over the age of 60 years. Only two RCTs assessed mortality, but no decrease was found in 30-day [36] or 1-year mortality [35] after the intervention. No differences regarding HRQoL were found [32, 37]. However, there is a lack of consensus regarding the most effective exercise type [38], the optimal dose of exercise [39] or the best moment to implement the exercise intervention (prehabilitation vs. rehabilitation) [40, 41]. In this regard, the combination of exercise with other interventions such as nutritional or mental support and behavior modification before surgery (i.e., multimodal prehabilitation) may not provide additional benefits to multimodal rehabilitation, as showed in a recent Cochrane Review [41]. However, the authors concluded that the low number of included participants and studies (only 250 patients among three RCTs) summed to their methodological heterogeneity might have limited the certainty of their conclusions so more and larger studies are needed to gather evidence. On the other hand, adherence to these programs is often inconsistently reported, and there are no clear recommendations on how to increase it [42]. Previous studies have shown that enrollment in exercise trials and adherence to exercise is negatively associated with older age [43, 44]. Some commonly reported barriers include physical symptoms related to cancer or its treatment (e.g. fatigue, peripheral neuropathy, comorbid health conditions, impaired mobility), psychological impact of cancer diagnosis, many hospital appointments, lack of information, lack of social support, and other constrains regarding time, costs, access and guidance [44, 45]. Low-cost and easily accessible programs that can be carried out at home and that are supported and guided by professionals (via direct supervision, written materials or by phone) may improve adherence to exercise [44, 46]. Therefore, the design of these programs should be adapted according to the characteristics of the population studied, the patient’s individual level of performance, the proposed outcomes and patient’s preferences [5, 47].

There is still a lack of knowledge on the benefits of exercise in older and more vulnerable patients, who are precisely those with the highest risk of complications and the greater loss of functional independence and HRQoL after CRC treatment. For this reason, we aim to study the effects of an individualized home-based multicomponent exercise program, supervised by a clinical exercise physiologist through telephone calls, on functional capacity and HRQoL in older adults undergoing elective CRC surgery when compared to usual care. Our primary hypothesis is that the exercise program improves functional capacity and HRQoL of older patients with CRC compared to usual care. The secondary aims will be to investigate the effect of the exercise program on physical performance, surgical complications and hospital readmissions, the prevalence of frailty, anxiety and depression, sarcopenia and cancer-cachexia, as well as the effects on physical fitness and inspiratory muscle function in comparison to usual care. Furthermore, the intervention’s safety and feasibility will be studied by registering patient’s adverse events and adherence to the program.

## Methods

### Study design and ethical approval

This study is a non-pharmacological, randomized, parallel-controlled, observer-blinded trial organized by the Health Research Institute Gregorio Marañón of Madrid, Spain. The study design, protocols and informed consent procedures were approved by the Medical Ethics Committee of *Hospital General Universitario Gregorio Marañón* (HGUGM) *(Madrid, Spain*) (ref.18/2021) and registered in clinicaltrials.gov (NCT05448846). The present study protocol will be conducted following the SPIRIT (Standard Protocol Items: Recommendations for Interventional Trials) statement and in accordance with the ethical guidelines of the Declaration of Helsinki [48]. The study will be carried out in the health care area of the HGUGM (Madrid, Spain) over a 3-year period.

### Study participants, screening and recruitment

Patients will be screened, informed, and included in the study at the HGUGM, Madrid, Spain. All patients will be provided a written informed consent. CRC patients aged 75 or older will be recruited at the geriatric outpatient clinic after the completion of a comprehensive geriatric assessment (CGA). The trial inclusion criteria will be: I) being 75 years or older, II) confirmed CRC diagnosis, III) being included in the surgical waiting list, and IV) being able to communicate, and able and willing to provide informed consent. The trial exclusion criteria will be: I) dismissal for surgery, II) any active limitation which affects adherence to the study procedures like terminal disease, myocardial infarction, or fractures in any limb (within the last three months before study participation), inability to walk or severe dementia (i.e., scoring Mini-Mental State Examination ≤ 18 points). Patients will be previously informed about the program’s content, study aims and randomization and about the role of care providers and research staff during participation. An overview of the study participant’s flow diagram is shown in Fig. 1.

**Fig. 1 Fig1:**
[figure not shown]
Flow diagram of the study

### Randomization and blinding

Patients who fulfill the inclusion criteria and accept to participate will be randomly assigned (1:1) to an intervention (IG) or control group (CG) following a computer-generated (Sealed Envelope Ltd. 2021) allocation sequence using a fixed block size of 6. The allocation sequence and resulting patient assignment will be concealed from study members involved in participants’ enrollment and assessment. Patients will be notified about allocation consignment by the study member involved in the intervention delivery, who will advise to participants not to discuss about their treatment assignment with blinded staff. Participants and care providers will be not blinded to the treatment group. By contrast, data collection and analysis will be performed by researchers blinded to the group allocation of the patients.

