### Intervention group (IG)

In addition to usual care received by the CG, patients in the IG will complete an individualized home-based multicomponent exercise program, supervised through telephone calls by a clinical exercise physiologist specialized in dealing with older patients, who is part of the local care team.

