### Sample size and statistical power

A priori sample size is calculated by estimating the difference between groups in the change in the quality scale of life (EORT QLQ-C30) from diagnosis to 3 months after discharge. A systematic review with meta-analysis pooling 25 clinical trials with a total of 547 cancer patients older than 70 years reported a mean ± standard deviation for global health status of 57.4 ± 23 points in the EORT QLQ-C30 scale [90]. If a difference of 10 points on this scale is considered clinically significant [60], using a two-sided sample t-test at the 5% level of significance with a statistical power (1-β) of 80%, we need to analyze a total of 166 patients. Mortality rate for patients over 74 years of age undergoing CRC surgery at the HGUGM is 4% (unpublished data). Assuming a conservative one-year mortality rate of 20% and an additional drop-out rate of 25% of the patients, we will need around 250 patients (125 per group). Considering a standard deviation of 16.3 points in the Barthel index based on data collected during the CGA for CRC patients conducted during the usual clinical practice at the HGUGM, this sample will be suitable for detecting a 10-points difference between groups, which is larger than the minimal clinically important difference for a geriatric population [91].

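### A fixed, published block size of 6 would make up to about a quarter of assignments certain if earlier assignments leaked to recruiting staff; varying the size is a cheap improvement

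*Protocol article*

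**What the plan says.** Randomization and blinding sets 1:1 assignment from a computer-generated "allocation sequence using a fixed block size of 6". The abstract describes one site: "This randomized, controlled, observer-blinded, single-center trial aims to randomize 250 patients". No stratification factor is mentioned, so there appears to be a single list. That is inferred from silence in a condensed article.

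The same section states the safeguard: "The allocation sequence and resulting patient assignment will be concealed from study members involved in participants’ enrollment and assessment". The member who delivers the intervention, not the enroller, tells patients their arm and advises them not to discuss it with blinded staff. Data collection and analysis are done by blinded researchers.

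Three further statements bear on how well the safeguard can hold:

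- On blinding: "Participants and care providers will be not blinded to the treatment group".
- On recruitment, patients are "recruited at the geriatric outpatient clinic after the completion of a comprehensive geriatric assessment" (Study participants, screening and recruitment).
- On the exercise physiologist, "who is part of the local care team" (Intervention group).

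The Control group section adds that the geriatric team gives assessment-guided care as part of usual care, and that the physiologist also advises control patients. Usual care goes to both arms.

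**The concern.** With one list and a constant block size that is now public, block boundaries follow from counting randomised patients. Once three patients in a block have gone to one arm, the rest of that block is determined. Protection therefore depends on enrolling staff not learning past assignments.

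The article places recruitment and unblinded care in the same clinical setting. The physiologist, who sees patients of both arms, works in the local care team. The advice to patients not to talk to blinded staff does not bind unblinded care providers. If 250 patients were enrolled evenly over the three-year study period (an assumption), accrual would be 250/36 = 6.9 a month, or roughly one block a month, which is easy to follow.

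If a recruiter could foresee an arm, the timing or approach of a frailer patient might be adjusted to it. The groups would then differ before treatment. Adjustment handles the measured part of such a difference but not the unmeasured part.

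**Working it through.** The article gives no predictability figure, so there is none to reproduce.

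**Inputs.** Block size 6, ratio 1:1 (3 + 3 per block) and planned N 250, all from the article. The share of past assignments an observer knows is not in the article and is varied below.

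**1. Certain assignments, all earlier ones known.** There are C(6,3) = 20 equally likely blocks. An assignment is certain once one arm has its three places filled.

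| Certain assignments in the block | Blocks out of 20 |
|---|---|
| 1 | 12 |
| 2 | 6 |
| 3 | 2 |

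Mean = (12×1 + 6×2 + 2×3)/20 = 30/20 = 1.5 of 6 = 25%. The closed form for a block of 2m agrees: 2m/(m+1) = 6/4 = 1.5. By position, the probability of being certain is 0.1 for the fourth patient, 0.4 for the fifth and 1 for the sixth, which sums to 1.5.

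**2. Over the trial.** 250 = 41×6 + 4. In the last, incomplete block only the fourth place can be certain, with probability 2/20 = 0.1. Expected number = 41×1.5 + 0.1 = 61.6, and 61.6/250 = 24.6%.

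**3. Best guess, all earlier ones known.** Guessing the arm with more places left is right with probability 0.5, 0.6, 0.6, 0.7, 0.7 and 1.0 at positions 1 to 6. The sum is 4.1, and 4.1/6 = 68.3%, against 50% by chance.

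**4. Partial knowledge.** Suppose boundaries are known and each past assignment is known independently with probability q. Certainty then needs all three filled places of one arm to be known, so the share in full blocks is 0.25×q³.

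| q | Share certain |
|---|---|
| 1 | 25% |
| 0.75 | 0.25×0.422 = 10.5% |
| 0.50 | 0.25×0.125 = 3.1% |
| 0.25 | 0.25×0.0156 = 0.4% |
| 0 (as the plan intends for enrolling staff) | 0% |

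Simulation gave the same values for q from 0.25 to 1.

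**5. Effect of varying the block size.** 1,000 trials of 250 patients were simulated. The observer knows every past assignment and the set of sizes, but not their order.

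| Block sizes | Known with certainty | Best guess correct |
|---|---|---|
| 6 (plan) | 24.6% | 68.2% |
| 4, 6 | 5.4% | 69.3% |
| 4, 6, 8 | 2.4% | 68.1% |
| 6, 8, 10 | 1.5% | 66.4% |

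Varying the size removes most of the certainty and hardly changes guessing.

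**The case against.** The strongest reply is that concealment is specified and the roles are separated. The sequence and the assignments are withheld from enrollers and assessors, someone else tells patients their arm, and patients are asked to keep it from blinded staff. Nothing in the article says that an unblinded care provider or the physiologist enrols patients. This stands. A leak is plausible from the setting but is not documented.

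A reader might infer that a quarter of assignments in this trial are simply predictable. The article does not support that: the figure is a ceiling that needs full knowledge of past assignments, and it is zero where concealment works.

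A reader might also count the 68% guessing rate as a harm that varied blocks would remove. The simulation shows otherwise.

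Nor is it right that nothing could be done in analysis. The Statistical analysis section adjusts for baseline differences and known prognostic factors, which covers measured imbalance. Response bias in patient-reported outcomes is a separate matter that block size does not affect.

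What remains is that the fixed size gives away more than it needs to if the safeguard slips, and that this can be avoided at almost no cost.

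**Conclusion.** This is a conditional, avoidable risk to concealment, and the remedy is a cheap improvement. The article contains no contradiction on this point and shows no breach. If earlier assignments became fully known near recruitment, 1.5 of 6 assignments on average, about 62 of 250, would be certain in advance. Under partial knowledge the share is about 10% (q = 75%) or 3% (q = 50%).

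These figures assume one unstratified list, known block boundaries and, for the partial cases, independent leakage of each assignment. Strata unknown to the observer would make tracking harder.

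**What to change.** For any allocations not yet used, have someone independent of enrolment generate a new list with randomly varying block sizes, for example 4, 6 and 8. Start it at a block boundary, and keep the sizes undisclosed until enrolment closes. Keep the present concealment of past assignments from enrolling staff, since it remains the main protection.

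The work is limited to regenerating the unused part of the list. The downside is slightly more possible imbalance when recruitment stops: at most half a block, so 4 patients with a block of 8 against 3 with a block of 6. The article gives no recruitment status; if no allocations remain, there is nothing to regenerate.

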## Interventions

### Control group (CG)

Participants randomly assigned to the control group will receive the usual care, which includes the Enhanced Recovery for Abdominal Surgery (ERAS) by the surgery department [49, 50]. This includes oral and written information on diet, avoiding sedentary lifestyle and breathing exercises with a spirometer, among other items that try to assure an early post-operative recovery. The participation of the geriatric team includes the CGA-guided intervention, mostly focused on the management of frailty and other geriatric syndromes, such as malnutrition, functional impairment, cognitive decline or depression and quality of life. In addition, the clinical exercise physiologist will give participants general advice about the positive effects of PA and will encourage them to reduce sedentary lifestyle.

### Intervention group (IG)

In addition to usual care received by the CG, patients in the IG will complete an individualized home-based multicomponent exercise program, supervised through telephone calls by a clinical exercise physiologist specialized in dealing with older patients, who is part of the local care team.

#### Exercise intervention

The Consensus on Exercise Reporting Template (CERT) is followed to provide elemental information about the exercise intervention [51]. The exercise intervention will be separated into I) pre-operative phase (prehabilitation), lasting from patient’s enrollment to hospital admission for CRC surgery, II) perioperative phase, from CRC surgery to patient’s discharge from hospital, and III) post-operative phase (rehabilitation), extending up to 12 weeks after CRC surgery. According to leading guidelines on exercise prescription for older adults [52], the exercise program will be tailored to the functional capacity of the patients. Thus, patients will be classified into 4 different groups depending on their Short Physical Performance Battery (SPPB) score, as follows: I) person with disability (SPPB score 0 to 3); II) frail person (SPPB score 4 to 6); III) pre-frail person (SPPB score 7 to 9); and IV) robust person (SPPB score 10 to 12) (see below: *Physical Performance*). The SPPB score will be the decision rule for determining the starting level of the program, which will be reviewed at subsequent face-to-face training sessions by the clinical exercise physiologist. A total of three face-to-face training sessions will be conducted individually at baseline (at own home for adjusting program to the environment of the patient), during hospitalization (once early mobilization of the patient is indicated), and one month after CRC surgery in the hospital setting. In these face-to-face training sessions, the clinical exercise physiologist will provide the corresponding education materials, guidance and motivation to complete the exercise program, observe exercise performance, correct exercise technique, and give feedback to the patients. The educational materials include an informative notebook with the explanations of the exercise program, an exercise diary and audiovisual material. Moreover, patients will receive instructions on how to complete the exercise diary for recording exercise sessions (e.g., exercise modality, repetitions, duration, intensity) of each training session.

The home-based multicomponent exercise program will involve 2 weekly training sessions aimed at improving strength and balance (resistance training) and 2 weekly training sessions aimed at improving cardiorespiratory fitness through brisk walking (endurance training), which will be complemented with daily inspiratory muscle training (IMT). Patients will be asked to complete resistance and endurance training sessions on alternate days, scheduled along the week according to their preferences.

